**Methods:**

This is a prospective cohort study, with an anticipated sample size of 240 patients (120 patients in the surgical group and 120 patients in the nonsurgical group). We will collect baseline data, including demographic, clinical, and radiological information, as well as data from patient-reported questionnaires. Patients will be followed up at 3, 6, 12, and 24 months after treatment, and survival status will be assessed every 3 months. The primary outcome is the overall survival period. Prognostic factors associated with overall survival will be analyzed by univariate and multivariate Cox proportional hazards regression. Odds ratios with 95% CIs will be presented. Statistical significance is set at *P*<.05.

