## Methods

### Study Design

This study is a prospective cohort study. We will compare the treatment outcomes of surgical and nonsurgical methods for SMLC in a real-world clinical scenario. The study will enroll 240 patients (120 patients in the surgical group and 120 patients in the nonsurgical group) from June 1, 2022, to June 30, 2027. The patients will be visited postoperatively at 3, 6, 12, and 24 months. The study is due to be completed on June 30, 2029.

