### Treatment

A surgical decision is made following the advice of our institutional multidisciplinary treatment team for spinal metastasis. There are 3 indications for surgery at our center: severe yet drug-resistant local pain, progressive neurological dysfunction, and emerging or latent spinal instability. Otherwise, patients are referred for nonsurgical treatment.

In the surgical group, patients are given surgical treatment, neurological rehabilitation, and adjuvant therapies (ie, SBRT and antitumor drugs). In this setting, we have established a synchronized workflow for surgery-based multimodality therapy instead of the conventional step-by-step schedule. A synchronized workflow means that neurological rehabilitation is incorporated and commenced right before the surgery and that SBRT and antitumor drugs are started early and simultaneously during the process of rehabilitation.

In the nonsurgical treatment group, patients are treated with adjuvant therapies exclusively, including radiotherapy, chemotherapy, targeted therapy, immunological therapy, etc. Considering the existence of various adjuvant modalities, this study will only enroll patients who receive both locoregional radiotherapy and antitumor drugs.

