#### Secondary Outcomes

Secondary outcomes include the following:

The progress-free survival period, defined as the time after the start of antitumor therapies until disease progression.Recovery of SMLC-related symptoms, defined as the relief of locoregional pain, which is measured by visual analogue scale (VAS) values, and the recovery of neurological status, which is assessed using the American Spinal Injury Association (ASIA) score. Immediate improvement in VAS and ASIA scores is assessed before discharge.Recovery of self-care performance, assessed using the Karnofsky Performance Scale (KPS) score and the Eastern Cooperative Oncology Group (ECOG) performance score.Quality of daily life, assessed by the Short Form 36 Health Survey Questionnaire.

Other outcomes for evaluation include complications in antitumor treatment. Surgical complications are rated according to the system proposed by Clavien et al [22], whereas toxicity of radiotherapy and antitumor drugs is graded using the National Cancer Institute’s Common Toxicity Criteria for Adverse Events (version 5.0). The endpoint of the study is the death of the recruited patient. The primary outcome is assessed by the endpoint of the study, whereas secondary and other outcome metrics are assessed at each visit.

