#### Exposure Measures

The exposure measures of interest include demographic variables, clinical data, and treatment-related factors. Demographic variables include age, gender, height, weight, and ethnicity. Clinical data are composed of health care factors (comorbidity, smoking status, family history of tumors); tumor factors (pathology, gene detection, tumor segments, and metastatic status); radiological variables (computerized tomography, magnetic resonance imaging, x-ray, positron emission tomography–computerized tomography, and degree of epidural spinal cord compression); and clinical variables, which include onset time, general status (KPS, ECOG score), neurological function (ASIA score), pain (VAS value), and ambulatory status. Treatment-related factors include operation approach, operation time, blood loss, postoperative hospital stay, adjuvant therapies, etc.

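### The early pain and neurology reading is set at discharge, which has no fixed time and is undefined for nonsurgical patients, so it should not be tested between groups

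*Protocol article*

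**What the plan says.** Secondary Outcomes in the protocol article lists relief of local pain (VAS) and neurological recovery (ASIA) as one secondary outcome, and sets its early reading by an event: "Immediate improvement in VAS and ASIA scores is assessed before discharge". The same section has secondary outcomes measured at every visit as well, so VAS and ASIA are also read at 3, 6, 12 and 24 months.

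Two places say what those visits are counted from. Study Design: "The patients will be visited postoperatively at 3, 6, 12, and 24 months". The Methods paragraph of the Abstract: "Patients will be followed up at 3, 6, 12, and 24 months after treatment".

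Under Treatment, the surgical group has an operation, rehabilitation, SBRT and antitumor drugs. The nonsurgical group has no operation, and for it "this study will only enroll patients who receive both locoregional radiotherapy and antitumor drugs". The only hospital stay named anywhere is in Exposure Measures, among the treatment-related factors: "operation approach, operation time, blood loss, postoperative hospital stay, adjuvant therapies".

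Statistical Analysis gives a one-sided two-sample t test and chi-square or Fisher tests for comparing groups. It names no outcome or time point for them, and mentions no adjustment for when a measurement was taken.

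**The concern.** A comparison of early symptom relief needs both groups to be read at the same distance from the start of treatment. Discharge does not provide that. For a surgical patient it ends a postoperative stay whose length varies enough to be recorded as a variable. For a nonsurgical patient the article does not say which admission is meant, or whether there is one.

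Two things could follow. If the discharge values are tested between groups, a difference in elapsed time can appear as a difference in treatment effect. And nonsurgical patients treated without admission would have no value, so the comparison would rest on a subset selected by how care was delivered. At stake is how an early difference in pain or neurology would be read in a study whose stated purpose is to compare the two treatment strategies.

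**Working it through.** The plan gives no figure for this measure, so there is none to reproduce. The check sets the text side by side and then illustrates the possible size on assumed values.

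**Step 1: what the text fixes for each group**

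| Item | Surgical | Nonsurgical |
|---|---|---|
| Early VAS/ASIA reading (Secondary Outcomes) | before discharge | before discharge |
| Interval from start of treatment | none | none |
| Stay that ends in discharge (Exposure Measures, Treatment) | postoperative stay, recorded | none described |
| Next reading | 3 months | 3 months |
| Origin of the 3 months: Study Design | operation | undefined, as there is no operation |
| Origin of the 3 months: Abstract | after treatment | after treatment |

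Discharge is therefore the only time point before 3 months, and the article gives it a meaning for one group only.

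**Step 2: is a between-group test planned?** It is not spelled out for this value. It is implied by the comparative aim (Objective, Study Design) together with group tests in Statistical Analysis that exclude no secondary outcome.

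**Step 3: illustration of the timing effect.** All inputs are assumptions. Both groups follow the same VAS course, with fall by day t = 4 × (1 − exp(−t/τ)) points and τ = 7, 14 or 28 days. The true difference is 0 at any common time.

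- Day 7 against day 14: τ = 7 gives 2.53 against 3.46, a difference of 0.93; τ = 14 gives 1.57 against 2.53, a difference of 0.95 before rounding; τ = 28 gives 0.88 against 1.57, a difference of 0.69.
- Day 7 against day 28: differences of 1.40, 1.88 and 1.64.
- Day 14 against day 3: differences of 2.06, 1.76 and 1.17.
- Equal discharge days: 0 in every case.

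The group read later looks better. The documents do not say which group that would be.

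**Step 4: would the planned test pick up such a difference?** Suppose a spurious difference of 1 point in the tested direction, an assumed SD of 2 to 3, and 96 to 120 patients per group (120 × 0.80 = 96, from the 80% follow-up rate in Sample Size and Study Timeline). The chance of a significant one-sided result at .05 is about Φ(1 / (SD × √(2/n)) − 1.645).

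- n = 96, SD = 3: Φ(2.309 − 1.645) = 0.75.
- n = 120, SD = 2: Φ(3.873 − 1.645) = 0.99.

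If the difference lies in the other direction, the one-sided test would not flag it.

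**Step 5: missing values.** If a share p of 96 nonsurgical patients is never admitted, 96 × (1 − p) have a discharge value: 96 at p = 0, 48 at p = 0.5, none at p = 1. The documents give no value for p.

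**The case against.** The strongest reply is that the article never says the discharge value will be tested between groups. A descriptive, within-group use fits the present text. That is correct, and it is why the point is conditional. Because nothing in Statistical Analysis rules the test out, one sentence is needed.

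Second, VAS and ASIA are also read at the scheduled visits, and the Abstract counts these from treatment, which has a meaning in both groups. This stands. A reader might infer from Study Design alone that the fixed visits are unusable for nonsurgical patients; the Abstract does not support that. The two wordings need to be reconciled, and the visits are then the remedy.

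Third, Multimedia Appendix 1 holds the visit timeline and is not shown. It may define an early time point. The body text nevertheless sets discharge, so an appendix with a common day would have to be reconciled with it.

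Fourth, a reader might infer that the discharge reading favours surgery because it compares a finished local treatment with an unfinished one. The documents do not support this. Surgical patients also receive SBRT and drugs, started during rehabilitation, and these may equally be incomplete at discharge. No length of stay, rate of outpatient treatment or speed of relief is given. If relief truly comes sooner after surgery, an early reading at a common time would show a real early difference.

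Finally, a common time point would not turn the comparison into a clean treatment effect. Under Treatment, severe pain and progressive neurological dysfunction are indications for surgery, so the groups can be expected to differ at baseline on the very measures being compared. This also stands, and the fix allows for it.

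**Conclusion.** The point holds in a limited form. The stated rule places the early VAS and ASIA reading at an event with no set time from treatment start and no definition for nonsurgical patients. A between-group test of that value would mix any treatment difference with differences in timing and in who has a value. The size and direction of the bias are unknown. The illustrated 0.7 to 0.95 points (day 7 against day 14) and 1.4 to 1.9 points (day 7 against day 28) rest wholly on assumed pain courses and discharge days, and the figure is 0 if discharge times are equal. Those numbers show that the effect could matter, not that it occurs.

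The scope is modest: the early reading of one secondary outcome. The later VAS and ASIA visits remain usable once their origin is settled. A reader might infer that the main comparison is weakened too; it is not, because overall survival does not depend on this reading.

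**What to change.** 1. State that the pre-discharge VAS and ASIA are reported descriptively within group, with no between-group test. Report the number of patients with a value and the days from treatment start to the reading.
2. Make the 3-month visit the first between-group comparison of VAS and ASIA. Count it in both groups from one time zero, such as the start of antitumor therapy already used for overall survival under Primary Outcome, and say whether the operation counts as that start. Bring Study Design and the Abstract into line on this.
3. Adjust that comparison for baseline VAS or ASIA, because pain and neurological dysfunction help decide who has surgery. Adjustment reduces this confounding but does not guarantee its removal.
4. Optionally, collect VAS at one fixed early interval from the same time zero in both groups, using the online interviews accepted under Strengths and Limitations. This covers pain only; ASIA would still have no early comparison.

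The cost is protocol wording and, if item 4 is taken up, one remote question per patient. The study gives up a between-group claim of immediate improvement, and patients who die before 3 months will not contribute to the first comparison, so their number should be reported by group. Enrollment has begun, so item 4 in particular is best settled soon.

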As our understanding of the molecular biology of lung cancer increases, many mutated targets are being identified, including the epidermal growth factor receptor (EGFR), anaplastic lymphoma kinase, ROS1, BRAF V600E mutation, etc [6,7,27,28]. Targeted drugs can act directly on these specific mutations and diminish tumor cells. Dohzono et al [29] compared the median OS of patients with SMLC receiving or not receiving EGFR tyrosine kinase inhibitors and found the former group enjoyed a longer OS period (21.4 months vs 6.1 months). In recent years, the application of some immunotherapeutic drugs has proven to be effective [7]. The concept of immunotherapy is to introduce specific blockers to inhibit some immunological signaling paths that are related to the development and metastasis of tumors. Currently, anti-PD-1 and anti-PD-L1 antibodies have been recognized as the choice of care for some advanced lung cancers after the failure of first-line cytotoxic therapy [30]. Borghaei et al [28] found that the median OS period of PD-L1(+) patients who received specific targeted blockers was longer than that of PD-L1(–) patients (17.7 months vs 10.5 months). Furthermore, systematic use of bone-targeted agents (eg, bisphosphonates and denosumab) has significantly reduced devastating spinal-related events, such as paralysis and loss of self-care ability [31].

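### Complications are graded by presumed cause on two scales, one usable only in operated patients, so the comparison of toxicity between groups depends on attribution (minor)

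*Protocol article*

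**What the plan says.** The harms outcome is described at the end of Secondary Outcomes in the protocol article, after the listed secondary outcomes: "Other outcomes for evaluation include complications in antitumor treatment". Two grading rules follow. Surgical complications are rated on the Clavien scale. By contrast, "toxicity of radiotherapy and antitumor drugs is graded using the National Cancer Institute" criteria, that is, CTCAE v5.0. These outcomes are to be assessed at every visit.

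The Treatment section states what each group receives. In the surgical group, "patients are given surgical treatment, neurological rehabilitation, and adjuvant therapies (ie, SBRT and antitumor drugs"). The timing is deliberately overlapping: "SBRT and antitumor drugs are started early and simultaneously during the process of rehabilitation". For the nonsurgical group, "this study will only enroll patients who receive both locoregional radiotherapy and antitumor drugs".

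Neurological status, pain, self-care and quality of life are secondary outcomes in their own right, for example "the recovery of neurological status, which is assessed using the American Spinal Injury Association (ASIA) score". Data Management and Supervision adds that a separate team monitors adverse events, without naming a scale, and that outcome assessors are blinded to treatment.

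**The concern.** The study exists to compare surgery-based with nonsurgical treatment, and the article expects its results to support a surgical strategy. Readers will want to set that against harm in the two groups. Using each scale for its own modality is ordinary when treatments follow one another. Here they overlap by design, so the scale an event reaches depends on a judgement about its cause, and surgery is an available cause in only one group. In addition, both grading rules are tied to treatment. An event caused by the spinal disease itself therefore belongs to neither, although in this population it may be among the most serious things that happen to a patient.

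**Working it through.** The document gives no complication rates and states no figure for this outcome, so there is nothing to reproduce. The check sets the stated rules side by side.

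1. **Which scale can apply to whom.** The surgical group has surgery, SBRT and antitumor drugs, so both scales apply. The nonsurgical group has radiotherapy and drugs, so CTCAE alone applies. CTCAE is thus shared by the groups, and the Clavien scale is not.

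2. **Whether cause can be separated.** The Treatment section replaces a step-by-step schedule with a synchronized one, in which SBRT and drugs begin during rehabilitation. The Introduction reports that radiotherapy is conventionally timed after the operation partly to avoid wound problems. The document itself therefore links radiotherapy to wound healing. A wound breakdown or new deficit while SBRT and drugs are running could reasonably be called surgical, treatment-related or both.

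3. **Effect on the shared scale.** In the surgical group, let T be the number of patients with a grade 3-5 event clearly due to radiotherapy or drugs. Let A be the number whose only such event could be assigned to either cause. The group's CTCAE count then lies anywhere from T (all ambiguous events called surgical) to T + A (all called toxicity). With 120 patients planned, each reassigned patient moves the proportion by 1/120 = 0.0083, or about 0.8 percentage points. A is not known. In the nonsurgical group, no event can leave the count by being called surgical. Attribution to the underlying disease is possible in both groups.

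4. **Events due to neither treatment.** New paralysis from uncontrolled disease is neither a surgical complication nor radiotherapy or drug toxicity, so neither rule grades it. Previous Studies, in background on bone-targeted agents, refers to "devastating spinal-related events, such as paralysis and loss of self-care ability".

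5. **Where such events would still be seen.** A new deficit can lower the ASIA score, loss of self-care can worsen KPS or ECOG, and pain and quality of life are covered by VAS and SF-36. Clinical visits are at 3, 6, 12 and 24 months (Abstract), which leaves 12 - 6 = 6 months between the second and third. The mean survival times assumed in Sample Size and Study Timeline, 9 and 11 months, both fall in that gap. A patient who becomes paralysed and dies between visits may contribute no worsened score.

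6. **Blinding.** Rating an event as a surgical complication requires knowing that the patient was operated on, which sits awkwardly with blinded outcome assessors. Grading without regard to cause eases this but does not remove it, since a wound reveals the operation.

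**The case against.** The strongest reply is that no error has been shown. A surgical scale for surgical events and CTCAE for toxicity is a normal pairing, complications are only an other outcome, and the article promises no comparison of total harm. Attribution rules, event definitions and reporting windows are commonly left to the full protocol, forms or SAP, none of which is shown. Data Management and Supervision says that rules for assessing outcomes will be drawn up, and its adverse event monitoring is not limited by cause. The sentence introducing the harms outcome need not be an exhaustive list.

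Much of this stands. It keeps the point minor, and the absence of attribution rules from the article is not itself a finding. What remains is that the split by cause is a rule the article states, combined with overlapping treatments that it also states. More detailed attribution rules would make the split more consistent, but the CTCAE comparison would still depend on attribution.

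Two stronger readings are tempting and are not supported:

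- A reader might infer that harm cannot be compared between the groups at all. Radiotherapy and drug toxicity is on CTCAE in both, and death from any cause determines the primary outcome in both.
- A reader might infer that the harms of not operating are left out of the study. They are outside the complications outcome only. ASIA, VAS, KPS, ECOG and SF-36 are not restricted to one group and can record decline, even though several are framed as relief or recovery.

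It is also fair to object that a common grading scale does not make the groups comparable. Patients are sent to surgery for refractory pain, worsening neurology or instability, so an any-cause rate will also reflect those baseline differences.

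**Conclusion.** The point holds in a limited form. Complications are graded by attributed cause on two scales, one of which can apply only to operated patients. Because treatments overlap in the surgical group, its CTCAE tally depends partly on how events are attributed, and the article states no common, cause-independent measure of overall complications. Deterioration due to the spinal disease is not counted as a complication, though visit scores can show it.

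The size cannot be computed without event rates, and none are given. A reader might also infer a bias in favour of surgery. That is not established: calling ambiguous events surgical lowers the group's toxicity tally, but calling them toxicity raises it. The conclusion assumes that the two grading rules are applied as written and that some events in the overlap period have an uncertain cause. Severity is minor.

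**What to change.** Grade every adverse event in both groups on CTCAE v5.0 whatever its presumed cause, explicitly including wound events and new or worse neurological deficit. Report the proportion of patients with any grade 3-5 event over the same window from treatment start in both groups, with the same adjustment for baseline differences as is used for the other group comparisons. Keep the Clavien rating as an additional description of the surgical group.

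The cost is wording in the protocol and forms. CTCAE is already in use, and no extra visit or change to treatment is involved. The downsides are that surgical events are graded twice, patients enrolled since June 2022 need regrading from records, and the surgical group's reported grade 3-5 rate may rise. The change removes the dependence on attribution. It does not remove the baseline differences between the groups.

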### Sample Size and Study Timeline

In this study, we plan to compare the overall survival (OS) time between the two groups and explore its prognostic factors. The sample size calculation was based on the survival time and estimation of influencing factors. According to an unpublished retrospective study performed at our center and previous literature [20,21], the average OS time was 11 (SD 4) months in the surgical group and 9 (SD 3) months in the nonsurgical group. Assuming an overall Type 1 error (α) of .05 and Type II error (β) of .1, we need 66 patients in each group. Additionally, there are 12 predictive factors we plan to analyze in the prediction model. According to the sample size estimation method for multivariable regression models, 100 cases in each group are needed (the ratio of surgical to nonsurgical group is 1:1). Considering a final follow-up rate of 80%, a minimum of 120 patients will be required for each group. There were approximately 25 patients undergoing surgery per year at our center; therefore, we plan to enroll the patients over the next 5 years. Since more patients are treated nonsurgically than surgically, all nonsurgical patients treated during the first 5 years will be enrolled.

The study duration is estimated to be 7 years to ensure that all recruited patients are followed up for 2 years. Each visit’s timeline and tasks are presented in Multimedia Appendix 1.

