### Statistical Analysis

Statistical analysis will be performed using SPSS for Windows (version 20; IBM Corp). The Lilliefors test will be used to examine whether the data are normally distributed. Data will be presented as percentages, mean (SD), or median (range) accordingly. The 1-tailed unpaired Student *t* test and Pearson *χ*^2^ test (or the Fisher exact test) will be used to make comparisons between different groups. The OS and progress-free survival curves will be plotted using the Kaplan-Meier method, and a comparison of the two groups will be performed via the log-rank test. The influencing factors will be analyzed by univariate and multivariate Cox proportional hazards regression. Statistical significance is set at *P*<.05. The survival prediction model will be established by multivariate Cox regression models and the Kaplan-Meier survival curves. The predictive ability of the final model will be evaluated using the Harrell concordance index (C-index) and calibration curves.

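### The tests named for pain, neurological, performance and quality-of-life scores would, at the 12- and 24-month visits, compare only patients still alive: small groups selected by survival that may differ by treatment

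*Protocol article*

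**What the plan says.** Study Design sets the schedule: "The patients will be visited postoperatively at 3, 6, 12, and 24 months". The Secondary Outcomes section lists VAS pain, ASIA neurological status, KPS and ECOG performance and SF-36 quality of life, and says that "secondary and other outcome metrics are assessed at each visit". It adds that VAS and ASIA improvement is also assessed before discharge, and that "The endpoint of the study is the death of the recruited patient".

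Statistical Analysis assigns Kaplan-Meier curves and the log-rank test to overall and progression-free survival. For everything else it names a one-tailed unpaired t test and a chi-square or Fisher exact test, which "will be used to make comparisons between different groups". It attaches no outcome or visit to these tests and does not say how a patient who has died enters a comparison at a later visit.

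Sample Size and Study Timeline gives the survival inputs: "the average OS time was 11 (SD 4) months in the surgical group and 9 (SD 3) months in the nonsurgical group".

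**The concern.** A patient who has died has no VAS, ASIA, KPS, ECOG or SF-36 score. A t test or chi-square test on the scores available at a visit is therefore a test among survivors. That matters little while nearly everyone is alive, but it matters once most patients have died, and more so if the two groups die at different rates.

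The outcomes at issue are closely tied to survival. The Discussion cites a study concluding that survival in this disease depends on genotype and on neurological and personal status, and neurological and performance status are among the secondary outcomes here. Survivors of a group with heavier mortality would then tend to be a more favourable selection, and the group difference in scores would mix treatment effect with selection. The direction cannot be known in advance: the sample size assumes longer survival with surgery, while a systematic review cited in the Discussion found the reverse (median 7.5 v 8.5 months).

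**Working it through.** **Step 1: are the survival inputs the plan's working figures?** The inputs are means 11 and 9 months, SDs 4 and 3, and "Type 1 error (α) of .05 and Type II error (β) of .1". The common SD is √[(4² + 3²)/2] = √12.5 = 3.54. Then n per group = (1.960 + 1.282)² × (16 + 9) / (11 − 9)² = 10.51 × 25/4 = 65.7, which rounds up to 66. The article states that "we need 66 patients in each group", so its figure reproduces with a two-sided α (one-sided gives 54). The enrolled number is 120 per group.

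**Step 2: survival at each visit.** The article gives a mean and SD but no distribution, so the shape is an assumption and a range is shown. For visit time t, mean m and SD s:

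- Normal: S(t) = 1 − Φ((t − m)/s). At 12 months, 1 − Φ(0.25) = 0.401 and 1 − Φ(1) = 0.159.
- Lognormal: σ² = ln(1 + s²/m²), μ = ln m − σ²/2, S(t) = 1 − Φ((ln t − μ)/σ).
- Gamma: shape (m/s)², scale s²/m.
- Exponential, figures read as means: S(t) = exp(−t/m). At 12 months, exp(−12/11) = 0.336 and exp(−12/9) = 0.264.
- Exponential, figures read as medians: S(t) = 2^(−t/m).

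Expected alive, surgical v nonsurgical:

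| Model | 3 months | 6 months | 12 months | 12 months, of 120 | 24 months, of 120 |
|---|---|---|---|---|---|
| Normal | 98% v 98% | 89% v 84% | 40.1% v 15.9% | 48 v 19 | 0.1 v 0.0 |
| Lognormal | 100% v 100% | 94% v 86% | 33.6% v 14.7% | 40 v 18 | 1.0 v 0.1 |
| Gamma | 100% v 100% | 92% v 85% | 35.8% v 15.5% | 43 v 19 | 0.6 v 0.0 |
| Exponential (mean) | 76% v 72% | 58% v 51% | 33.6% v 26.4% | 40 v 32 | 13.5 v 8.3 |
| Exponential (median) | 83% v 79% | 69% v 63% | 46.9% v 39.7% | 56 v 48 | 26.4 v 18.9 |

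The first three models use the stated means and SDs; the exponential ones drop the SDs and serve as a sensitivity check. Mortality by 12 months, pooled over groups, is 72%, 76%, 74%, 70% and 57% in table order. The ratio of surgical to nonsurgical survivors at 12 months is 2.3 to 2.5 with the stated SDs and 1.2 to 1.3 with exponential curves.

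**Step 3: what selection alone could do (illustration).** Assume the normal model, no treatment effect on the score, and a correlation ρ between score and survival time. The mean standardised survival time among those alive is φ(z)/[1 − Φ(z)], which is 0.964 at z = 0.25 (surgical) and 1.525 at z = 1 (nonsurgical). The spurious 12-month group difference is ρ × (1.525 − 0.964) = ρ × 0.56 SD: 0.11 SD for ρ = 0.2 and 0.28 SD for ρ = 0.5. The correlations are assumed; the article gives none.

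**Step 4: precision.** For a true difference of 0.5 SD, two-sided α 0.05 and the normal approximation, power is Φ(0.5/√(2/120) − 1.96) = 97% with 120 v 120. With 48 v 19 it is Φ(0.5/√(1/48 + 1/19) − 1.96), about 46%.

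**The case against.** The strongest reply is that the criticised comparison is not written down. The article says that scores are collected at each visit and, separately, names generic group tests that could equally be meant for baseline or perioperative variables. Collecting 24-month data is not an error, and a rule for deaths could sit in a fuller protocol or analysis plan. This stands as far as it goes. A reader might infer that the plan commits to testing survivors at 12 and 24 months; the article does not say so. What remains is that the only tests it fixes for these outcomes use observed scores, so following them at the late visits gives a survivor comparison by default.

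Second, the size depends on the survival shape. A reader might take 40% v 16% at 12 months and nobody at 24 months as the plan's prediction. The article supports only the range: its literature includes a cohort with a median of 12 months and a median of 21.4 months with EGFR inhibitors, which fits poorly with near-zero 24-month survival, at least for some patients. The conclusion that more than half of each group has died by 12 months survives every model tried; a large imbalance between groups does not.

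Third, an early assessment almost free of survivor selection already exists, before discharge, for VAS and ASIA. That stands and is part of the remedy.

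Fourth, an obvious repair, a chi-square test on the proportion alive and improved, would do harm. The Treatment section reserves surgery for refractory pain, progressive neurological dysfunction or instability. Nonsurgical patients will tend to start with less deficit, those with none cannot improve, and all of these would count as failures, which favours surgery by construction. That stands too.

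**Conclusion.** The concern holds in limited form. If the named tests are applied to symptom, function and quality-of-life scores at 12 and 24 months, they compare survivors. On the article's own inputs these are about 34% to 47% of the surgical group and 15% to 40% of the nonsurgical group at 12 months. At 24 months they range from almost none to about 26 v 19 of 120. Such comparisons are small and selected by survival that may differ by group, with bias of unknown direction.

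This rests on the stated means and SDs, on assumed distributional shapes, and on the absence from the article of any rule for deaths. Overall and progression-free survival are analysed by time-to-event methods and are not affected. The pre-discharge assessment is little affected. The 3-month visit is little affected under the stated means and SDs (about 98% or more alive in both groups); under exponential survival it would be 76% v 72% or 83% v 79%, so numbers alive should be shown there too. Since only secondary outcomes are involved, the point should be corrected but does not threaten the primary analysis.

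**What to change.** Make the main between-group comparison of VAS, ASIA, KPS, ECOG and SF-36 the 3-month visit, supplemented by the existing pre-discharge assessment for VAS and ASIA. Adjust each comparison for the patient's baseline value. VAS, ASIA, KPS and ECOG are listed under Exposure Measures, and the Abstract says that patient-reported questionnaires are collected at baseline.

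Report the 12- and 24-month values descriptively among survivors, beside the number alive in each group, without a treatment test. If death is to enter a comparison, rank it as the worst outcome in a baseline-adjusted analysis and show survival and symptom components separately. Do not use an unadjusted alive-and-improved proportion.

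The cost is a few lines of analysis wording and a regression in place of the simple tests for these outcomes; no new data are needed. The downsides are that late symptom scores get no formal treatment comparison, and that any composite mixes survival with symptoms. Baseline adjustment also does not by itself remove confounding by the indication for surgery, which is a separate matter.
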